# APPENDIX

Participant ID # \_\_\_\_\_

Visit Date \_\_\_\_/\_\_\_\_/\_\_\_\_

## Appendix: STUDY COMPLETION

*To be completed by study coordinator*

1. Date of final study visit: \_\_\_\_ / \_\_\_\_ / \_\_\_\_  
Day Month Year
2. Participant notified regarding end of active protocol study participation?  
☐ YES ☐ NO
3. Date of last-known study intervention: \_\_\_\_ / \_\_\_\_ / \_\_\_\_  
Day Month Year
4. Primary reason for terminating participation in the study:
  - ☐ Completed study
  - ☐ Not eligible\*
  - ☐ Participant was determined after enrollment to be ineligible (provide comments) \_\_\_\_\_\*
  - ☐ Participant withdrew consent
  - ☐ In the principal investigator's opinion, it was not in the participant's best interest to continue (provide comments) \_\_\_\_\_
  - ☐ Adverse event (If checked, complete the AE form)
  - ☐ Death
  - ☐ Lost to follow-up
  - ☐ Other (specify): \_\_\_\_\_
  - ☐ Unknown

\*If participant determined to be ineligible due to CES-D score, give participant the DEBRIEFING – DEPRESSION letter.

Comments:

Investigator Signature: \_\_\_\_\_

Date: \_\_\_\_\_

DAY-MONTH-YEAR

Participant ID # \_\_\_\_\_

Visit Date \_\_\_\_/\_\_\_\_/\_\_\_\_

---

## ID Migraine Screener

---

*To be completed by participant if migraine headache reported*

**During the last 3 months, did you have any of the following with your headaches?\***

1. You felt nauseated or sick to your stomach when you had a headache?

☐ Yes    ☐ No

2. Light bothered you (a lot more than when you don't have headaches)?

☐ Yes    ☐ No

3. Your headaches limited your ability to work, study, or do what you needed to do for at least 1 day?

☐ Yes    ☐ No

Investigator Signature: \_\_\_\_\_

Date: \_\_\_\_\_

DAY-MONTH-YEAR

Participant ID # \_\_\_\_\_

Visit Date \_\_\_\_/\_\_\_\_/\_\_\_\_

## PHYSICAL EXAM - HEALTH STATUS REASSESSMENT

*To be completed by clinician if indicated in Health Status Reassessment*

This participant has self-reported a change in his or her health status and needs to be reassessed for adverse events and ability to participate in the study. Refer to HEALTH STATUS REASSESSMENT form for details and complete the form below based on findings.

| Category                                               | Normal or Abnormal                                                                                            | If abnormal, describe below |
|--------------------------------------------------------|---------------------------------------------------------------------------------------------------------------|-----------------------------|
| General Appearance                                     |  Normal
 Abnormal
 Not Examined |                             |
| Musculoskeletal                                        |  Normal
 Abnormal
 Not Examined |                             |
| Extremities/
Skin                                   |  Normal
 Abnormal
 Not Examined |                             |
| Neurological
(dermatomes,
myotomes,
reflexes) |  Normal
 Abnormal
 Not Examined |                             |
| Other, specify:
_____                               |  Normal
 Abnormal
 Not Examined |                             |

I certify this patient is:

- ☐ Able to continue study
  - ☐ Temporarily unable to continue in the study at this time due to a self-limited medical condition
    - ☐ Reassess health status in \_\_\_\_\_ days / weeks. (complete Protocol Deviation Form and Adverse Event Form)
  - ☐ Unable to continue in the study due to a serious change in medical status (complete Adverse Event Form, Protocol Deviation Form and Study Completion Form)
- ☐ I have recommended the participant seek medical care from his or her personal physician.

Investigator Signature: \_\_\_\_\_

Date: \_\_\_\_\_

DAY-MONTH-YEAR

Participant ID # \_\_\_\_\_

Visit Date \_\_\_\_/\_\_\_\_/\_\_\_\_

## Appendix: SERIOUS ADVERSE EVENT

*To be completed by study coordinator*

1. SAE onset date: \_\_\_\_/\_\_\_\_/\_\_\_\_  
Day Month Year
2. SAE stop date: \_\_\_\_/\_\_\_\_/\_\_\_\_  
Day Month Year
3. Location of serious adverse event: \_\_\_\_\_
4. Was this an unexpected adverse event? ☐ Yes ☐ No
5. Brief description of participants with no personal identifiers:  
Sex: ☐ F ☐ M Age: \_\_\_\_\_  
Diagnosis for study participation: \_\_\_\_\_
6. Brief description of the nature of the serious adverse event (attach description if more space is needed):  
\_\_\_\_\_
7. Category of the serious adverse event:
 

|                                                                     |                                                                                                                                                  |
|---------------------------------------------------------------------|--------------------------------------------------------------------------------------------------------------------------------------------------|
|  Death: Date of death _____
(dd/mm/yyyy) |  Congenital anomaly/birth defect                                                                                         |
|  Life threatening event                     |  Required intervention to prevent permanent impairment – important medical event based upon appropriate medical judgment |
|  Hospitalization – inpatient or prolonged   |  Other: _____                                                                                                            |
|  Disability/incapacity                      |                                                                                                                                                  |
8. Intervention type:
 

|                                                                                |
|--------------------------------------------------------------------------------|
|  Medication or nutritional supplement (specify): _____ |
|  Device (specify): _____                               |
|  Surgery (specify): _____                              |
|  Behavioral/lifestyle (specify): _____                 |

Investigator Signature: \_\_\_\_\_

Date: \_\_\_\_\_

DAY-MONTH-YEAR

Participant ID # \_\_\_\_\_

Visit Date \_\_\_\_/\_\_\_\_/\_\_\_\_

## Appendix: ADVERSE EVENTS

*To be completed by study coordinator*

Has the participant had any adverse events (AE) during this study?

☐ Yes (if yes, please list all adverse events below.)

☐ No

| Adverse Event
(Refer to CTCAE Grading and
Attribution Scales) | Start Date | Stop Date | Severity
Grade* | Attribution** | Action Taken | Outcome of AE | Expected | Serious
Adverse Event | Reportable to
IRB? Y/N | Initials |
|---------------------------------------------------------------------|------------|-----------|--------------------|---------------|--------------|---------------|----------|--------------------------|---------------------------|----------|
| 1.                                                                  |            |           |                    |               |              |               |          |                          |                           |          |
| 2.                                                                  |            |           |                    |               |              |               |          |                          |                           |          |
| 3.                                                                  |            |           |                    |               |              |               |          |                          |                           |          |
| 4.                                                                  |            |           |                    |               |              |               |          |                          |                           |          |
| 5.                                                                  |            |           |                    |               |              |               |          |                          |                           |          |
| 6.                                                                  |            |           |                    |               |              |               |          |                          |                           |          |
| 7.                                                                  |            |           |                    |               |              |               |          |                          |                           |          |
| 8.                                                                  |            |           |                    |               |              |               |          |                          |                           |          |
| 9.                                                                  |            |           |                    |               |              |               |          |                          |                           |          |
| 10.                                                                 |            |           |                    |               |              |               |          |                          |                           |          |
| 11.                                                                 |            |           |                    |               |              |               |          |                          |                           |          |
| 12.                                                                 |            |           |                    |               |              |               |          |                          |                           |          |

Investigator Signature: \_\_\_\_\_

Date: \_\_\_\_\_

## Appendix: ADVERSE EVENTS - ATTRIBUTES

### \*\*ATTRIBUTION

| Severity Grade*                                                   | Attribution**                                                                                            | Action Taken                                                                                                               | Outcome of AE                                                                                                                                                                                             | Expected      | Serious Adverse Event                         |
|-------------------------------------------------------------------|----------------------------------------------------------------------------------------------------------|----------------------------------------------------------------------------------------------------------------------------|-----------------------------------------------------------------------------------------------------------------------------------------------------------------------------------------------------------|---------------|-----------------------------------------------|
| 1 Mild
2 Moderate
3 Severe
4 Life-threatening
5 Death | 1 Clearly Unrelated
2 Doubtfully Related
3 May be Related
4 Likely Related
5 Clearly Related | 1 None
2 Discontinued permanently
3 Discontinued temporarily
4 Reduced dose
5 Increased dose
6 Delayed dose | 1 Resolved, no sequela
2 AE still present, no treatment
3 AE still present, being treated
4 Residual effects present, not treated
5 Residual effects present, treated
6 Death
7 Unknown | 1 Yes
2 No | 1 Yes (If YES, complete SAE form)

2 No |

| RELATIONSHIP                                                 | ATTRIBUTION | DESCRIPTION                                              |
|--------------------------------------------------------------|-------------|----------------------------------------------------------|
| Unrelated to investigational agent/intervention  | Unrelated   | The AE is clearly NOT related to the intervention |
|                                                              | Unlikely    | The AE is doubtfully related to the intervention  |
|                                                              | Possible    | The AE may be related to the intervention         |
|                                                              | Probable    | The AE is likely related to the intervention      |
| Related to investigational agent/intervention    | Definite    | The AE is clearly related to the intervention     |

Grade refers to the severity of the AE. The CTCAE displays Grades 1 through 5 with unique clinical descriptions of severity for each AE based on this general guideline:

- Grade 1 Mild; asymptomatic or mild symptoms; clinical or diagnostic observations only; intervention not indicated.
- Grade 2 Moderate; minimal, local or noninvasive intervention indicated; limiting age-appropriate instrumental ADL\*.
- Grade 3 Severe or medically significant but not immediately life-threatening; hospitalization or prolongation of hospitalization indicated; disabling; limiting self care ADL\*\*.
- Grade 4 Life-threatening consequences; urgent intervention indicated.
- Grade 5 Death related to AE.

A Semi-colon indicates 'or' within the description of the grade.

A single dash (-) indicates a grade is not available.

Investigator Signature: \_\_\_\_\_

Date: \_\_\_\_\_

[figure not shown]

*Place participant ID label here*

Participant ID # \_\_\_\_\_

Visit Date \_\_\_\_/\_\_\_\_/\_\_\_\_

**Investigator Signature:** \_\_\_\_\_

**Date:** \_\_\_\_\_

[figure not shown][figure not shown]

Case Report Forms  
Final Version 5.0  
21 April 2016

Place participant ID label here

Participant ID # \_\_\_\_\_

Visit Date \_\_\_\_/\_\_\_\_/\_\_\_\_

## PROTOCOL DEVIATION FORM

Did this participant have any protocol deviations? ☐ Yes ☐ No

| Description of Protocol Deviation | Deviation Category* | Deviation Code** | Date Deviation Occurred | Date IRB Notified (if applicable) | Principal Investigator's Signature | Date Signed |
|-----------------------------------|---------------------|------------------|-------------------------|-----------------------------------|------------------------------------|-------------|
|                                   |                     |                  |                         |                                   |                                    |             |
|                                   |                     |                  |                         |                                   |                                    |             |
|                                   |                     |                  |                         |                                   |                                    |             |
|                                   |                     |                  |                         |                                   |                                    |             |
|                                   |                     |                  |                         |                                   |                                    |             |

Investigator Signature: \_\_\_\_\_

Date: \_\_\_\_\_

## PROTOCOL DEVIATION CATEGORY AND CODE

### \*DEVIATION CATEGORY

|           |                     |                |                            |                          |
|-----------|---------------------|----------------|----------------------------|--------------------------|
| A. Safety | B. Informed Consent | C. Eligibility | D. Protocol Implementation | E. Other, specify in log |
|-----------|---------------------|----------------|----------------------------|--------------------------|

### \*\*DEVIATION CODES: Numbers listed by the sample protocol deviations

|                                                                                                                                                                                                                                                                                                                                                                                                                                                                                       |                                                                                                                                                                                                                                                                                                                                                                                                                                                                                                                                                                        |
|---------------------------------------------------------------------------------------------------------------------------------------------------------------------------------------------------------------------------------------------------------------------------------------------------------------------------------------------------------------------------------------------------------------------------------------------------------------------------------------|------------------------------------------------------------------------------------------------------------------------------------------------------------------------------------------------------------------------------------------------------------------------------------------------------------------------------------------------------------------------------------------------------------------------------------------------------------------------------------------------------------------------------------------------------------------------|
| Safety (Category A) 
 
1. Not reporting an SAE within 24 hours
 
2. Laboratory tests not done
 
3. AE/SAE is not reported to IRB
 
4. Other, specify in log
 
                                                                                                                                                                                                                                                | Eligibility (Category C) 
 
1. Participant did not meet eligibility criterion
 
2. Randomization of an ineligible participant
 
3. Participant randomized prior to completing baseline assessment, etc.
 
4. Randomization and/or treatment of participant prior to IRB approval of protocol
 
5. Other, specify in log
 
                                                                                                                                                              |
| Informed consent (Category B) 
 
6. Failure to obtain informed consent
 
7. Consent form used was not current IRB-approved version
 
8. Consent form does not include updates or information required by IRB
 
9. Consent form missing
 
10. Consent form not signed and dated by participant
 
11. Consent form does not contain all required signatures
 
12. Other, specify in log
 
 | Protocol implementation (Category D) 
 
1. Failure to keep IRB approval up to date
 
2. Participant receives wrong treatment
 
3. Participant seen outside visit window – intervention & clinical outcomes
 
4. Participant seen outside visit window – physiological outcomes
 
5. Use of unallowable concomitant treatments
 
6. Prescribed dosing outside protocol guidelines
 
7. Missed assessment
 
8. Missed visit
 
9. Other, specify in log
 
 |

Investigator Signature: \_\_\_\_\_

Date: \_\_\_\_\_

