- **Per-Protocol Analysis (PPA):** For the PPA we will exclude study participants who: 1) fail to attend 4 out of 6 treatment sessions; and 2) receive prohibited concomitant interventions (section 5.3.3), or 3) develop an exclusionary medical condition while on study protocol. Finally, we will assess how comparable estimated parameters vary between ITT and PPA analyses. Below we describe our analytic plans for specific outcome measures.

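### The per-protocol exclusion list does not cover wrong treatment or ineligibility at randomization, though the deviation form codes both

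*Supplement*

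**What the plan says.** Section 9.5 (Detailed Analytic Approach, Per-Protocol Analysis) holds the only definition of the per-protocol set. It opens: "For the PPA we will exclude study participants who: 1) fail to attend 4 out of 6 treatment sessions". The remaining two grounds read: "receive prohibited concomitant interventions (section 5.3.3), or 3) develop an exclusionary medical condition while on study protocol". There is no general clause for other major deviations. The same paragraph undertakes to compare the parameter estimates from the ITT and per-protocol analyses. Section 9.5 makes ITT the primary analysis.

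The Case Report Forms v5.0 (Protocol Deviation Category and Code) and the Protocol Deviations SOP give each deviation a category and number. Category C (eligibility) includes C1, a participant who did not meet an eligibility criterion, and C2, "Randomization of an ineligible participant". Category D (protocol implementation) includes D2, "Participant receives wrong treatment". The deviation form records the date of each event.

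**The concern.** A per-protocol analysis is meant to describe people who met the entry criteria and received the treatment they were assigned. Here the attendance ground counts sessions attended, whatever was delivered at them. The medical ground reaches only conditions that develop after entry. Neither ground removes someone who received another arm's treatment or who should not have been randomized.

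Eligibility carries particular weight in this trial. Section 9.2 relies on a modified clinical prediction rule to select the patients most likely to respond. A per-protocol set that keeps people who failed that rule no longer describes the intended population.

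The planned ITT versus per-protocol comparison is also at stake. Every wrongly treated or ineligible participant kept in both sets makes the sets more alike, so agreement between the two estimates says less about the influence of protocol departures. With no rule fixed beforehand, the choice could also be made after the treatment codes are known.

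**Working it through.** The plan states no figure on this point, so there is none to reproduce. The main check sets the codes beside the rule.

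**Step 1: codes against the three exclusion grounds**

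| Deviation code | Covered by Section 9.5? |
|---|---|
| D5, unallowable concomitant treatment | Yes, second ground |
| D8, missed visit | In part, through attendance |
| D2, wrong treatment | No: "fail to attend 4 out of 6 treatment sessions" concerns attendance, so wrong-arm sessions count |
| C1/C2, ineligible | No: the third ground is "or 3) develop an exclusionary medical condition while on study protocol", so it does not reach ineligibility present at randomization |

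**Step 2: does another section close the gap?**

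- Sections 10.3.3 and 10.3.4 send deviations to the Steering Committee, which considers whether the participant continues, the impact on procedures and the next steps. Neither mentions an analysis set.
- The Study Completion form can record that a participant was found ineligible after enrollment. It sets no analysis rule.
- The SOP covers definition, coding and reporting of deviations, not their use in analysis.

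So the gap stands on the text.

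**Step 3: scale for wrong treatment**

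Inputs from Section 9.2: 54 participants per arm, assumed effect size d = 0.5, NPR standard deviation 2.5. The implied contrast is 0.5 × 2.5 = 1.25 points. The number k of wrongly treated participants is not in the documents. I assume k = 1, 3 or 5 in one manual-therapy arm, each given sham at every session.

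Diluted contrast = 1.25 × (1 − k/54):

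- k = 1: 1.25 × 53/54 = 1.23, a shift of 0.02
- k = 3: 1.25 × 51/54 = 1.18, a shift of 0.07
- k = 5: 1.25 × 49/54 = 1.13, a shift of 0.12

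The standard error of the contrast, ignoring attrition and baseline adjustment, is 2.5 × √(2/54) = 0.48. The largest shift is 0.12/0.48, about a quarter of a standard error.

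If the same number in the sham arm also received the manual therapy, the factor becomes 1 − 2k/54. The contrast is then 1.20, 1.11 or 1.02, and the shifts double.

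No comparable sum can be done for C1/C2. The documents give neither a count nor an expected effect in ineligible participants.

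**The case against.** The case against has several parts.

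**Stakes.** ITT is primary, the RCT component is described as exploratory Phase II, and no stated hypothesis rests on the per-protocol result. This stands, and it limits the importance of the point.

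**Size.** A code on a form headed as sample deviations is no evidence that the event happens. Even the assumed worst case in one arm moves the estimate by 0.12 points, against a clinically meaningful NPR difference of 2 points in Section 9.5. This also stands. A reader might infer that agreement between ITT and per-protocol results would be largely built in and so give false reassurance. Without deviation rates, the documents do not support that.

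**Existing safeguards.** Eligibility is checked on a full checklist at Visit 1, before treatment is randomized at Visit 2. A participant found ineligible may be stopped and then fail the attendance ground. That helps only if discovery comes early. Late discovery leaves the person in the set.

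**The SOP's definition.** The SOP defines a deviation as having no substantive effect on the value of the data. That fits poorly with listing wrong treatment among the codes, and it does not settle how such a participant is analysed.

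Two stronger readings are tempting.

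- **Removing out-of-window outcome visits.** Codes D3 ("Participant seen outside visit window – intervention" and clinical outcomes together) and D4 ("Participant seen outside visit window – physiological outcomes") are also absent from the exclusion list. But D3 does not separate treatment visits from outcome visits. The post-treatment window is itself inconsistent: 3 days ± 1 in Sections 3 and 9.1, but ± 2 days for physiological outcomes in Section 6.2.4, which also gives study days 23 to 25 for clinical outcomes. Those passages must be reconciled first. The SOP treats scheduling-related cases as minor, and no bias from a mistimed score has been shown.
- **Excluding anyone with a single wrong session.** The attendance ground, read as requiring four of six, tolerates two missed sessions. One session of another treatment withholds no more of the assigned treatment than one missed session does.

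**Conclusion.** The point holds for wrong treatment (D2) and for ineligibility at randomization (C1/C2). Both are recorded, neither removes a participant from the per-protocol set, and no other section does so. The conclusion about the rule rests on the text alone.

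The consequence is conditional. It arises only if such deviations occur, and the documents do not say how often they do. On the assumed range of 1 to 5 of 54 in one arm, the NPR contrast falls by 0.02 to 0.12 points, which is small beside its sampling error. For ineligible participants the size is unknown. The primary analysis is unaffected. This is a worthwhile tidying of a secondary analysis, with no threat to the trial's main conclusions.

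**What to change.** In Section 9.5:

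1. Exclude from the per-protocol set any participant coded C1 or C2.
2. Count only sessions of the assigned treatment toward the attendance criterion, so that a session coded D2 is treated as not attended.
3. Assign the set from the deviation log before the treatment codes are released. The log needs to supply only the code and date, not the arm.

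The second item works only if the attendance ground excludes on its own. The present punctuation, with *and* after the first ground and *or* before the third, could be read as requiring the first two grounds together, so it should be clarified in the same edit. That ambiguity is a separate matter: resolving it alone would leave the present gap open.

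The cost is a sentence or two in Section 9.5 and a slightly smaller per-protocol set. No new data are needed, because the deviation form already captures the codes and dates. The primary ITT analysis does not change.
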